### Randomization procedure

The randomization list will be computer-generated by a statistician from the Clinical Research Unit of *Henri Mondor University Hospitals* (Créteil, France) independent of the study, and uploaded in an online case report form (electronic CRF, eCRF—Cleanweb Telemedecine Technologies, France). The chief investigator of each center will connect to the eCRF via a web browser, fill in the participant characteristics and assign participants to their study group online. A unique allocation study number will be assigned to each study participant in sequential order (R00X format). Randomization will be perform at D-30, and each participant will be assigned to one of the two treatment groups: CONV group (Conventional Therapy) or GSC group (Guided Self-rehabilitation Contract). A confirmation email will be sent to the unblinded investigator of the coordinating center. As assessment visits will be conducted in only one of the four inclusion centers, randomization will not be stratified by center. Randomization will be stratified according to the initial voluntary symmetry score of the Sunnybrook Facial Grading Scale (ranging from 5 to 25), performed at D-30. To ensure comparability of patients with respect to their level of motor function (severity) at inclusion two ranges of score will be selected: [5-15] and [16-25] for stratified randomization. Blinding will be preserved until the database is frozen.

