### Statistical methods

#### Sample size

The required number of subjects has been determined to be 82, from preliminary data in literature: to our knowledge the sole RCT about rehabilitation in subacute/chronic stages of PFP (participants enrolled from 9 months into the onset of paresis) using SFGS included 50 participants, among whom only 24 benefited from rehabilitation (waiting list without any rehabilitation in the other group) [62].

In contrast with that trial, participants of the control group of the present study will benefit from an intervention (physiotherapy and/or speech therapy), which will be associated with the potential to improve clinical status. We thus hypothesize that there will be a minor improvement of + 10 points in the Sunnybrook composite score in that group. Based on that hypothesis and to demonstrate an improvement of + 20 points (with a standard deviation up to 13) for the experimental group, considering a 5% alpha risk (bilateral test) and a statistical power of 90%, we will include 41 patients per group for 36 analyzed (assuming a 10% loss of follow-up).

Regarding the secondary objectives, it should be noted that this sample size will be comparable to other reliability and validity studies for the FaCE scale (*n* = 67 to 122 patients; [47, 48, 59–61] and larger than the initial Sunnybrook validation study (*n* = 19; 12). Regarding reliability parameters such as the intraclass correlation coefficients (ICC) and for ICC values expected to be > 70%, the suggested sample size will allow estimating ICCs with an accuracy of ± 15% for two measures and ± 10% for three measures and more [63]. Strategies for achieving adequate participant accrual to reach the target sample size will involve communication on the study with ENT specialists, speech therapists and physiotherapists in the greater Paris area.

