#### Statistical analysis

Descriptive statistical analysis will be carried out to evaluate randomization groups in terms of demographic, and initial clinical and kinematic characteristics, including PFP cause, delay since injury, side of paresis, previous drug treatments, and comorbidities. Quantitative data will be described using means (± SD) or medians (with IQR), depending on the normality of distributions, and qualitative data will be reported as numbers or percentages.

Changes in the Sunnybrook Composite score between D1 and D180 will be evaluated by Student’s *t* test. No interim analysis has been planned. The primary outcome analysis will be performed using Intention to treat (ITT) analysis. Comparative analysis of quantitative values at J90 and J180 – including primary and secondary outcomes—will be performed with Student’s *t* tests for independent samples or with Mann–Whitney non-parametric tests, depending on conditions. Changes in quantitative values from inclusion to each assessment visit (D90-D1, D180-D1) will be compared taking into account the baseline data in case of baseline intergroup differences despite randomization. Within-group changes will be tested through Student’s *t*-tests for matched data or Wilcoxon Rank sum tests, depending on the conditions. Multiple linear regression models will be tested to identify independent predictors associated with the changes in quantitative parameters over time, including longitudinal analysis of random effects (mixed models).

Comparative analysis of binary parameters will be run through Chi-square or Fisher’s exact tests, depending on conditions. Multivariable analysis will be generated through logistic regression models. Intra- and inter-rater reliability studies will use frequencies of agreement, intraclass correlation coefficients, Cohen and Fleiss kappa coefficients and coefficients of variation. Spearman or Pearson coefficients will be calculated between scores on the various scales, depending on conditions. Complementary analyses on the primary outcome and all analyses regarding secondary outcomes will be performed in both ITT and per protocol (PP) populations to describe the excluded patients of the PP population and to evaluate the robustness of the results.

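### Randomisation is stratified by Sunnybrook voluntary symmetry class, but the stated primary t test leaves the stratum out; the likely cost is a modest loss of precision in the conservative direction

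*Protocol article*

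**What the plan says.** All references are to the protocol article.

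- **Randomization procedure:** "Randomization will be stratified according to the initial voluntary symmetry score of the Sunnybrook Facial Grading Scale", measured at D-30. The classes are fixed: "two ranges of score will be selected: [5-15] and [16-25] for stratified randomization". The stated purpose is comparability of the arms in severity at inclusion. No block size or other balancing method is given.
- **Statistical analysis, primary test:** the method named is Student's t test, in the sentence that opens "Changes in the Sunnybrook Composite score between D1 and D180 will be evaluated by". No stratum term appears there.
- **Statistical analysis, baseline:** changes from inclusion to each visit "will be compared taking into account the baseline data in case of baseline intergroup differences despite randomization". Adjustment is therefore conditional on what is observed, and the stratum is not mentioned. The regression and mixed models in the same section serve to identify predictors of change; they do not replace the primary test.
- **Sample size:** the control arm is expected to gain "10 points in the Sunnybrook composite score in that group". The other arm is put at "20 points (with a standard deviation up to 13) for the experimental group". The error rates, in per cent, are set by the words "considering a 5% alpha risk (bilateral test) and a statistical power of 90". The resulting target is given as "we will include 41 patients per group for 36 analyzed (assuming a 10% loss of follow-up".

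**The concern.** The stratum is a dichotomised component of the scale that supplies the primary outcome. If allocation is held balanced within each class, differences between classes cannot contribute to the difference between arms. A two-sample t test nevertheless counts those differences as error. Its standard error then overstates the true variability of the estimate, its confidence interval is too wide, and it rejects a true null hypothesis less often than the nominal 5%.

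The conditional adjustment does not close this gap. Stratification makes a visible imbalance on this factor unlikely, so the condition that would bring baseline into the analysis will seldom arise from it. Letting the observed data decide whether to adjust also leaves the primary model open until the data are seen.

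What is at stake is precision. By an exact t calculation, 36 analysed per arm gives 89.6% power, so the design has no spare margin.

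**Working it through.** **1. The plan's own figure.** Inputs from Sample size: difference 20 − 10 = 10, SD 13, two-sided 5%, power 90%.

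n per arm = 2 × (1.960 + 1.282)² × 13² / 10² = 35.5, rounded up to 36, as stated. With 10% loss, 36 / 0.9 = 40 per arm against 41 stated, which is within rounding. Exact t power is 89.6% at 36 per arm and 90.4% at 37.

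**2. Effect of omitting the stratum.** Let d be the difference in mean change between the two strata and p the share of patients in one of them. Neither is in the document. I take p = 0.5 and total SD 13, and assume allocation balanced within strata.

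- Share of variance explained by the stratum: R² = p(1 − p)d² / 13²
- Ratio of reported to true standard error: 1 / √(1 − R²)
- Real alpha of the unadjusted test: 2 × [1 − Φ(1.96 / √(1 − R²))]
- Standardised effect at 36 per arm: 10 / (13 × √(2/36)) = 3.264
- Power, unadjusted: Φ((3.264 − 1.96) / √(1 − R²))
- Power, stratum in the model: Φ(3.264 / √(1 − R²) − 1.96)

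Example, d = 5: R² = 0.25 × 25 / 169 = 0.037; ratio 1.019; alpha = 2 × [1 − Φ(1.997)] = 4.6%.

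| d (points) | SE ratio | Real alpha | Power, unadjusted | Power, with stratum |
|---|---|---|---|---|
| 0 | 1.000 | 5.0% | 90.4% | 90.4% |
| 2.5 | 1.005 | 4.9% | 90.5% | 90.6% |
| 5 | 1.019 | 4.6% | 90.8% | 91.4% |
| 7.5 | 1.044 | 4.1% | 91.3% | 92.6% |
| 10 | 1.083 | 3.4% | 92.1% | 94.2% |
| 15 | 1.224 | 1.6% | 94.5% | 97.9% |

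Simulation of 72 patients with blocks of 4 (assumed) agrees: unadjusted alpha is 4.9%, 4.5%, 3.4% and 1.8% at d = 0, 5, 10 and 15, and 4.9% to 5.2% with the stratum in the model. With unrestricted allocation within strata, the unadjusted test stays at about 4.8% to 5.1% whatever d is.

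**3. Which d is plausible.** Further assumptions: equal SDs σ at D1 and D180, correlation r between them, a median split, and a stratum score correlated 0.85 with the D1 composite. The SD of change fixes σ = 13 / √(2(1 − r)). Mean change falls by (1 − r) for each point of D1, and the two halves differ at D1 by 2 × √(2/π) × 0.85σ = 1.356σ. Hence d = 1.356 × 13 × √((1 − r)/2) = 17.63 × √((1 − r)/2). With the D1 composite in the model, the residual SD of change is 13 × √((1 + r)/2), and power is Φ(3.264 / √((1 + r)/2) − 1.96).

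| r | d | Real alpha, formula | Real alpha, simulation | Power, unadjusted | With stratum | With D1 composite |
|---|---|---|---|---|---|---|
| 0.3 | 10.4 | 3.2% | 3.2% | 92.3% | 94.6% | 98.2% |
| 0.5 | 8.8 | 3.7% | 3.6% | 91.7% | 93.4% | 96.5% |
| 0.7 | 6.8 | 4.2% | 4.2% | 91.2% | 92.3% | 94.3% |
| 0.9 | 3.9 | 4.7% | 4.4% | 90.6% | 91.0% | 91.7% |

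The powers are by formula. In simulation the gain is about 0.5 to 3 points for the stratum alone and up to about 6.5 with the D1 composite, against 0.4 to 2.3 and up to 5.9 here. Simulated alpha with the stratum in the model is 4.6% to 5.0%. At r = 0.9 I give more weight to the formula's 4.7%, since simulated rates carry sampling error.

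**The case against.** A reader might infer that the primary test is certainly run below its stated 5%. The document does not support that. It takes two conditions: balance forced within strata and a stratum that predicts change. No balancing method is described, although restricted allocation is the natural reading of stratification meant to secure comparable severity. Nor is any relation between stratum and change reported. The endpoint already subtracts D1, and eligibility requires stable chronic paresis, so r may be high and the effect close to nil. Real alpha falls to about 4% only when the strata differ by about 8 points in mean change, close to the whole 10-point treatment effect. On the other side, the composite is bounded at 100 and milder patients have less room to gain, so a change score need not be free of its baseline.

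It is also fair to say that an unadjusted test after stratified allocation is valid, and that balance, the stated aim of the stratification, is achieved without it. Both points stand, and they limit this to an efficiency point.

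A third objection is that the D1 composite does most of the work. This stands too: in the set-up above the stratum carries no information beyond D1, so adjusting for D1 alone restores nominal alpha. The stratum still belongs in the model as the factor used in randomisation.

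Finally, covariate lists are often left to an analysis plan, which is not shown. But the article does name the primary test and the condition for adjusting, and those are the statements at issue.

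**Conclusion.** The mismatch is real: the factor that structures the randomisation is absent from the stated primary test, and the imbalance-triggered adjustment does not reliably bring it in. Any resulting error is conservative. Type I error is not inflated, the treatment estimate is not biased, and by the planning formula power does not fall below the planned 90%.

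The size cannot be fixed from the document. Under the assumptions shown (balance within strata, median split, stratum score correlated 0.85 with D1, r from 0.3 to 0.9), real alpha is about 3.2% at the low end of r and 4.4% to 4.7% at the high end. The reported standard error is about 1% to 9% too large (1/√(1 − R²) with R² = 0.25 × 3.9²/169 = 0.023 and 0.25 × 10.4²/169 = 0.16). If the stratum does not predict change, alpha is 5.0% and nothing is lost. Importance lies between a minor point and one that should be acted on. Confidence is high that the stratum is missing from the stated test, moderate as to the size of the effect.

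**What to change.** In Statistical analysis, replace both the unadjusted t test and the conditional baseline adjustment with one prespecified linear model for the D1 to D180 change in the Sunnybrook composite. It should contain arm, the stratum as randomised (voluntary symmetry 5-15 against 16-25 at D-30) and the D1 composite. Report the adjusted difference with its 95% confidence interval as the primary result, and keep the t test as a supporting analysis if wanted. If the analysis plan already specifies such a model, bring the two documents into line.

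The cost is two degrees of freedom (residual 70 to 68 with 72 analysed) and a change of wording before the database is frozen. Both covariates are already collected under the study schedule, so conduct, visits and sample size are unaffected.

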### Study population

Eligible patients must be diagnosed with stable, chronic,—*i.e.* that occurred at least one year before inclusion—unilateral peripheral facial paresis, whatever its cause. To participate in the study, subjects must meet all other inclusion criteria and none of exclusion criteria listed in Table 1. Patients may be enrolled in this study as early as one year after onset for the following reasons: there is no consensus on the transition time to the chronic form of facial paralysis, mentioned from 6 months to two years depending on reports [60, 61]; it is often considered that most of the neurological recovery occurs within the first year after the onset even though there is no scientific evidence to date; in the same way it is considered that the further away from the onset of the facial paresis, the less the amount of conventional rehabilitation; patients are generally offered to start botulinum toxin injections from one year post onset of paresis and once these are started, it is rare for the patient to be willing to stop them, even temporarily. In Beurskens et al., 2006, it was also considered that patients 9–12 months from onset were in the chronic stage [62].

### Data management

All information required by the protocol will be entered in the eCRF. Data will be collected as they are obtained. Any missing data will be coded. Every site will have access to the eCRF via a web-based data collection system. Investigators will be given a document offering guidance on using this tool. Each investigator will be responsible for the accuracy, quality and relevance of all the data entered. An audit trail of all changes will be saved. The computer file used for this research is implemented in accordance with French (amended “Informatique et Libertés” law governing data protection) and European (General Data Protection Regulation – GDPR) regulations. The sponsor has obtained the authorization of the CNIL (“*Commission Nationale de l’Informatique et des Libertés*”, French Data Protection Agency) before implementing any of the data processing required to conduct the research. If a subject stops participating or withdraws consent, the data collected up to the date of cessation will be analyzed. If a subject is lost to follow-up, the investigator should make every effort to reconnect with the patient. Subjects who have prematurely stopped their participation in the research will not be replaced.

### Data monitoring

A Clinical Research Associate (CRA) appointed by the sponsor will be responsible for the proper processing of the study, for collecting, documenting, recording and reporting all handwritten data, in accordance with the Standard Operating Procedures applied within the ‘DRCI’ (Clinical Research and Innovation Department at *Assistance Publique-Hôpitaux de Paris*) and in accordance with Good Clinical Practices as well as with the statutory and regulatory requirements. Computerized quality control will be put in place for missing data detection and consistency of data timing. In case of incorrect filling out of the e-CRF, the investigator will be asked to correct.

### Harms

In this study involving human participants (as defined in category 2 of art. L1121-1 of the French Public Health Code), adverse events (serious or not) will not be notified to the sponsor. Notification will be implemented within the framework of the vigilance set up in usual care procedures. No data monitoring committee is needed.

### Audit

In accordance with Good Clinical Practice, the sponsor is responsible for obtaining the agreement of all parties involved in the research to ensure direct access to all research sites, source data, source documents and reports for quality control and audit purposes by the sponsor. Investigators will make the documents and individual data available to persons in charge of monitoring and quality control, in the event of an audit, in accordance with the legislative and regulatory provisions in force.

### Statistical methods

#### Sample size

The required number of subjects has been determined to be 82, from preliminary data in literature: to our knowledge the sole RCT about rehabilitation in subacute/chronic stages of PFP (participants enrolled from 9 months into the onset of paresis) using SFGS included 50 participants, among whom only 24 benefited from rehabilitation (waiting list without any rehabilitation in the other group) [62].

In contrast with that trial, participants of the control group of the present study will benefit from an intervention (physiotherapy and/or speech therapy), which will be associated with the potential to improve clinical status. We thus hypothesize that there will be a minor improvement of + 10 points in the Sunnybrook composite score in that group. Based on that hypothesis and to demonstrate an improvement of + 20 points (with a standard deviation up to 13) for the experimental group, considering a 5% alpha risk (bilateral test) and a statistical power of 90%, we will include 41 patients per group for 36 analyzed (assuming a 10% loss of follow-up).

Regarding the secondary objectives, it should be noted that this sample size will be comparable to other reliability and validity studies for the FaCE scale (*n* = 67 to 122 patients; [47, 48, 59–61] and larger than the initial Sunnybrook validation study (*n* = 19; 12). Regarding reliability parameters such as the intraclass correlation coefficients (ICC) and for ICC values expected to be > 70%, the suggested sample size will allow estimating ICCs with an accuracy of ± 15% for two measures and ± 10% for three measures and more [63]. Strategies for achieving adequate participant accrual to reach the target sample size will involve communication on the study with ENT specialists, speech therapists and physiotherapists in the greater Paris area.

#### Statistical analysis

Descriptive statistical analysis will be carried out to evaluate randomization groups in terms of demographic, and initial clinical and kinematic characteristics, including PFP cause, delay since injury, side of paresis, previous drug treatments, and comorbidities. Quantitative data will be described using means (± SD) or medians (with IQR), depending on the normality of distributions, and qualitative data will be reported as numbers or percentages.

Changes in the Sunnybrook Composite score between D1 and D180 will be evaluated by Student’s *t* test. No interim analysis has been planned. The primary outcome analysis will be performed using Intention to treat (ITT) analysis. Comparative analysis of quantitative values at J90 and J180 – including primary and secondary outcomes—will be performed with Student’s *t* tests for independent samples or with Mann–Whitney non-parametric tests, depending on conditions. Changes in quantitative values from inclusion to each assessment visit (D90-D1, D180-D1) will be compared taking into account the baseline data in case of baseline intergroup differences despite randomization. Within-group changes will be tested through Student’s *t*-tests for matched data or Wilcoxon Rank sum tests, depending on the conditions. Multiple linear regression models will be tested to identify independent predictors associated with the changes in quantitative parameters over time, including longitudinal analysis of random effects (mixed models).

Comparative analysis of binary parameters will be run through Chi-square or Fisher’s exact tests, depending on conditions. Multivariable analysis will be generated through logistic regression models. Intra- and inter-rater reliability studies will use frequencies of agreement, intraclass correlation coefficients, Cohen and Fleiss kappa coefficients and coefficients of variation. Spearman or Pearson coefficients will be calculated between scores on the various scales, depending on conditions. Complementary analyses on the primary outcome and all analyses regarding secondary outcomes will be performed in both ITT and per protocol (PP) populations to describe the excluded patients of the PP population and to evaluate the robustness of the results.

All missing or invalid data will be systematically sought for verification in patient charts. In addition to the analysis performed on complete cases without missing data for the primary outcome, sensitivity analysis will be performed using various methods of replacement of missing data, including the LOCF method (Last Observation Carry Forward), the worst-case assumption, and multiple account assignment by chained equations (MICE). Participants who terminate the study prematurely will not be replaced. All analyzes will be performed with Stata software v14.1 (StataCorp, College Station, TX, USA).

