### Outcome measures

To evaluate motor function beyond one year after facial nerve injury, the primary outcome measure will be the composite score of the Sunnybrook Facial Grading System. This scale, created by Ross et al. in 1996, assesses resting symmetry compared to the normal side for each third of the face through rating of resting symmetry, of symmetry of voluntary movements on a five-grade scale during five facial movements, and associated synkinesis. A composite score is then calculated, ranging from 0 (total paralysis) to 100 (normal) [12]. The French version of the SFGS was recently validated [45]. As stated above, the choice not to use House-Brackmann evaluation scales [11, 46] is in accordance with the fact that these scales are no longer recommended in research [10, 47, 48].

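### The primary change-score t test may be replaced by a baseline-adjusted comparison if the arms differ at baseline, with no trigger stated; one always-adjusted model should be named instead

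*Protocol article*

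**What the plan says.** All of this is in the protocol article.

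- **Primary outcome** (Outcome measures): "the primary outcome measure will be the composite score of the Sunnybrook Facial Grading System".
- **Named primary test** (Statistical analysis): "Changes in the Sunnybrook Composite score between D1 and D180 will be evaluated by" Student's t test. No covariate is mentioned.
- **Values at each visit** (same paragraph): "Comparative analysis of quantitative values at J90 and J180", with the primary outcome included, by t test or Mann–Whitney test. J180 is D180.
- **Conditional adjustment** (same paragraph): changes in quantitative values, with D90 minus D1 and D180 minus D1 listed explicitly, "will be compared taking into account the baseline data in case of baseline intergroup differences despite randomization". There is no threshold, test or model, and the primary outcome is not excluded.
- **Stratification** (Randomization procedure): "Randomization will be stratified according to the initial voluntary symmetry score of the Sunnybrook Facial Grading Scale", taken at D-30 in two bands, 5–15 and 16–25. The stratum is not named in the primary comparison.
- **Schedule** (Table 2): the Sunnybrook scale is recorded at D-30, D1, D90 and D180, so the D1 covariate is already collected.

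Multiple regression and mixed models are also mentioned, but for identifying predictors of change, not for estimating the primary treatment effect.

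**The concern.** D180 minus D1 in the Sunnybrook composite is the primary contrast, so the conditional sentence can be read as applying to it. Two different primary estimates are then possible, and the choice turns on a judgement about baseline imbalance that the article does not define.

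Three things are at stake:

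- **An open choice.** With no trigger fixed, the decision to adjust cannot later be shown to be independent of the result.
- **Conditional bias.** A change score subtracts the whole baseline value, whereas the expected D180 score moves by only a fraction r of it. If one arm starts higher by chance and no adjustment is made, regression to the mean shifts the change-score contrast.
- **Efficiency.** A change score uses baseline by subtraction but not as a covariate. Under the assumptions below, covariate adjustment has a smaller standard error, and the data for it are already in the schedule.

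**Working it through.** **Inputs.** From Sample size: control arm "there will be a minor improvement of + 10 points in the Sunnybrook composite score"; experimental arm +20, so a difference of 10; SD up to 13; two-sided alpha 5%; power 90%; 41 included and 36 analysed per group. Assumptions not in the article: 13 is the SD of the change, the D1 and D180 variances are equal, scores are normal, and the D1–D180 correlation r lies between 0.5 and 0.9.

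**1. The plan's own figure.** n per arm = 2 × 13² × (1.960 + 1.282)² / 10² = 35.5, so 36. This agrees with the article. Allowing 10% loss, 36 / 0.9 = 40 per arm against 41 stated, which is close enough. The standard error of the difference is 13 × √(2/36) = 3.06 points. Power at 36 per arm is 90.4% by the normal approximation and 89.6% by the noncentral t. The named t test and the sample size therefore agree.

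**2. Adjusting always.** Relative to the change score, the residual variance under analysis of covariance is (1 − r²) / [2(1 − r)] = (1 + r)/2. The effective SD is 13 × √((1 + r)/2). Power is by the noncentral t.

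| r | Variance ratio | Effective SD | SE (points) | Power at 36 per arm |
|---|---|---|---|---|
| change score | 1 | 13.00 | 3.06 | 89.6% |
| 0.5 | 0.75 | 11.26 | 2.65 | 96.0% |
| 0.7 | 0.85 | 11.99 | 2.82 | 93.7% |
| 0.8 | 0.90 | 12.33 | 2.91 | 92.4% |
| 0.9 | 0.95 | 12.67 | 2.99 | 91.0% |

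The variance saving runs from 25% at r = 0.5 to 5% at r = 0.9.

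If 13 is instead the SD of the score itself, the change SD is 13 × √(2(1 − r)) and the adjusted SD is 13 × √(1 − r²). Power by the normal approximation is then 78.8% against 92.8% at r = 0.3, 90.4% against 96.5% at r = 0.5, and 98.8% against 99.5% at r = 0.7. The direction is the same and the size depends on r.

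**3. Conditional bias when an imbalance goes unadjusted.** Bias = (1 − r) × k × s × √(2/36), where s = 13/√(2(1 − r)) is the score SD and k is the imbalance in standard errors.

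| r | s | Median imbalance (k = 0.6745) | k = 1.9 |
|---|---|---|---|
| 0.5 | 13.0 | 1.0 points | 2.9 points |
| 0.7 | 16.8 | 0.8 points | 2.3 points |
| 0.8 | 20.6 | 0.65 points | 1.8 points |

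The median column assumes simple randomisation. The k = 1.9 column is close to the worst case that a 5% baseline test would leave unadjusted.

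**4. The switching rule.** It was simulated with 100,000 trials per setting, 36 per arm, no stratification, and an assumed trigger of baseline p < 0.05 or p < 0.20, since the article gives none.

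| r | Type I error (trigger 0.05 / 0.20) | Power of the rule (0.05 / 0.20) | Power if always adjusted |
|---|---|---|---|
| 0.5 | 4.3% / 3.7% | 90.5% / 91.9% | 95.9% |
| 0.7 | 4.6% / 4.3% | 90.1% / 90.8% | 93.4% |
| 0.8 | 4.7% / 4.5% | 89.8% / 90.4% | 92.0% |

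Applied strictly, the rule is slightly conservative and recovers only part of the available power. When the p < 0.05 trigger fires, the adjusted and unadjusted estimates differ on average by about 3.5, 2.7 and 2.2 points at r = 0.5, 0.7 and 0.8, against a target of 10. If an analyst were free to report the smaller of the two p values, type I error would be about 7.2%, 6.8% and 6.3–6.6%.

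**The case against.** The case for leaving the plan alone is substantial.

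- **The primary test has its own sentence.** The t test on change is named without an alternative, and the conditional clause belongs to a general sentence on quantitative outcomes. This stands in part: the t test is clearly the default. But the general sentence lists D180 minus D1 and does not exclude the primary outcome, so the ambiguity remains.
- **The planned test is sound.** It is unbiased over randomisation, uses baseline by subtraction, and delivers about the stated power. This stands in full. The gain from adjustment is one of efficiency and depends on a correlation that the article does not give.
- **Stratification limits imbalance.** This is true in part. The D-30 voluntary symmetry score is one component of the composite, so large imbalances are less likely than under simple randomisation. It is used in only two wide bands, and resting symmetry and synkinesis also enter the composite.
- **The model and trigger could sit in an analysis plan that is not shown.** That excuses the missing detail. It does not excuse the rule itself, which this article states and which an analysis plan following it would inherit.

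A reader might also infer that there are three competing primary analyses, because the raw D180 values are to be tested too. The text does not support this: nothing puts the raw-value comparison forward as the headline result.

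**Conclusion.** The point holds as a should-fix improvement. The article leaves open, until the baseline data are seen, whether the primary estimate is adjusted for baseline, and it forgoes the precision of the D1 covariate unless an undefined trigger fires. With 13 read as the SD of change and equal variances, always adjusting would raise power from 89.6% to between 91.0% (r = 0.9) and 96.0% (r = 0.5). An imbalance left unadjusted shifts the estimate by a median of about 0.65 to 1.0 points for r from 0.8 to 0.5.

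Three stronger readings are tempting, and the documents do not support them:

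- **That the rule inflates type I error.** Strictly applied it does not (3.7–4.7% under the assumed triggers). A rate near 7% needs a free choice of the better p value, which the article does not describe. The undefined trigger only fails to rule it out.
- **That the estimate is materially biased.** The shifts of 1.8 to 2.9 points need an imbalance of 1.9 standard errors, which is near the worst case and not typical.
- **That the trial is underpowered or its primary test invalid.** On its own figures, with 13 as the SD of change, it is neither.

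**What to change.** In the Statistical analysis section, delete the clause that makes use of baseline conditional on observed group differences. Before unblinding, name one primary model: a linear regression of the D180 Sunnybrook composite on arm, D1 composite and randomisation stratum, fitted whatever the observed imbalance. Using the D1 to D180 change as the response gives the same treatment estimate, because the D1 score is in the model. State that D1 is the baseline, since the scale is also recorded at D-30.

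Label the unadjusted t test on change, and the t or Mann–Whitney comparison of D180 values, as supportive. Use the same baseline-adjusted model for the other quantitative outcomes measured at D1.

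The cost is a change of wording in the protocol or analysis plan. It needs no new data, visits or participants, and the sample size can stay as it is.
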